### Primary outcome

Functional change over 1 year as measured longitudinally by the ALS Functional Rating Scale (ALSFRS-R),^33^ a validated rating instrument for monitoring the progression of disability in patients with ALS that correlates with survival and quality of life.

### Secondary outcomes

#### Combined Assessment of Function and Survival (CAFS)

This analysis ranks clinical outcomes on the basis of survival and change in ALSFRS-R scores.^34^ Each patient’s outcome is compared with every other patient’s outcome, assigned a score, and the summed scores are ranked. The mean rank score for each treatment group can then be calculated.

#### Quality of life for patients: WHOQOL-BREF

A 26-item quality of life measure developed by the World Health Organisation and validated for use in pwALS.^35^

#### Health status: EQ-5D-3L

A standardised measure of health status, covering five areas with three scoring options for each, developed by the EuroQol Group in order to provide a simple, generic measure of health for clinical and economic appraisal.^36^ Preference-based utility weights will be applied to EQ-5D-3L responses using UK population-based values from the UK value set.^37^ Utility values range from 1-perfect health to 0 death, with negative scores indicating states worse than death. This will be completed by both patients and carers.

#### Respiratory function: slow vital capacity (SVC)

A measure of respiratory muscle strength shown to correlate with survival in ALS, taken by spirometry. Forced expiratory volume in 6 seconds (FEV6) will also be taken via spirometry. Participants will be supplied with handheld spirometers. Participants who are able to use a smartphone-reliant spirometer will take SVC and FEV6 measurements. Participants who cannot use a smartphone-reliant spirometer will take FEV6 measurements only. Both measurements are considered acceptable alternatives based on existing literature.^38^,^42^

#### Anthropometric assessments

Triceps skin fold, mid arm circumference and calf circumference measurements will be taken using standardised methods.^43^ Given the asymmetry in ALS, the mean values taken from both upper and lower extremities will be used. Fat mass and fat free mass will then be estimated. If outcomes are measured remotely, triceps skin fold will not be taken and calf circumference will be used as the primary method of fat mass and fat-free mass estimation.

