## Study outcomes

Participants will be followed up at week 1, month 1, month 3 and then at 3-month intervals until month 12 or until death if this is earlier. Survival status of each participant will be reassessed at the end of the study (between 12 and 35 months postrandomisation depending on when the patient was recruited). All outcome measures will be collected by a blinded assessor, except blood samples, calorie intake, adverse events (AEs) and acceptability of the intervention. Where clinic visits are not possible (eg, if shielding due to COVID-19), data will be collected at the participants’ home, either in person (if feasible), via video call, or via phone call if a video call is not possible. Where physical measures are to be collected via video or phone call, participants will be sent any equipment needed to complete these in advance of the appointment, as well as being directed to information about taking the measures in a separate section of the OptiCALS portal, including step-by-step videos. Training will also be provided by the blinded assessor prior to any measurements being taken. If neither a face-to-face nor remote follow-up appointment can be arranged, the questionnaire outcomes ALSFRS-R, WHOQOL-BREF, EQ-5D-3L, Healthcare Resource Use and Acceptability Questionnaire (intervention group only) can be self-completed by post or electronically via email.

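### Fat mass and fat-free mass appear to be estimated by different methods at remote and face-to-face visits, so change within a participant can be partly a change of method

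*Protocol article*

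**What the plan says.** Under Anthropometric assessments, the article states the default set: "Triceps skin fold, mid arm circumference and calf circumference measurements will be taken using standardised methods". It continues: "Fat mass and fat free mass will then be estimated". No equation is named. For remote assessments the rule changes: "If outcomes are measured remotely, triceps skin fold will not be taken and calf circumference will be used as the primary method" for estimating the two masses.

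Under Study outcomes, the schedule is repeated: "Participants will be followed up at week 1, month 1, month 3 and then at 3-month intervals until month 12". The mode of each visit depends on circumstances at the time: "Where clinic visits are not possible (eg, if shielding due to COVID-19), data will be collected at the participants’ home", and this may be "either in person (if feasible), via video call, or via phone call if a video call is not possible".

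Under Data analysis, secondary outcomes other than the time-to-event and combined rank outcomes follow the primary-outcome approach. That is a linear mixed model with time, treatment, their interaction and the minimisation variables as fixed effects, and centre as a random intercept. Mode of assessment is not among the listed terms. The Strengths and limitations box accepts that remote collection may be inaccurate for height, weight and spirometry; it does not mention body composition.

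**The concern.** The rule ties the estimation method to the visit mode, and mode is set visit by visit rather than once per participant. A single participant's series of fat mass and fat-free mass can therefore contain values from two estimators, which the stated model would treat as one variable. If the estimators do not agree on average, a move from clinic to remote assessment puts a step into the series that the model reads as change over time.

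This matters because the intervention aims to raise calorie intake and to maintain or increase weight, and these two measures show what kind of mass is kept or gained. Mode may also be related to function. The Introduction describes progressive weakness, and the Strengths and limitations box says remote access helps people for whom participation might otherwise not be feasible because of disability. If treatment slows decline, moves to remote assessment could be fewer in the intervention arm, and the artefact would then enter the treatment contrast.

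**Working it through.** The article states no effect size, standard deviation, power or method agreement for body composition, so there is no figure to reproduce. The check is a reading of the text followed by an illustration on assumed values.

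**Reading the text**

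1. Face to face: skin fold, mid arm and calf circumference are all available.
2. Remote: no skin fold, and calf circumference is the primary method. Naming it as primary for this case implies that it is not the primary method otherwise. This is the natural reading, but it is an inference.
3. Visits run from week 1 to month 12, and mode depends on whether a clinic visit is possible at that time, so a switch within a participant is possible.
4. The stated model has no mode term, and nothing shown requires one method per participant.
5. Calf circumference is in the measurement set in both modes.

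**Illustration (all inputs assumed)**

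Let d be the mean offset between methods, and p_C and p_T the shares of control and intervention participants who switch from face to face to remote.

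- Artefact in an arm's mean change = d × p
- Between-arm artefact = d × (p_T − p_C)
- Variance inflation with equal switching = 1 + d² × p × (1 − p) / SD²

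| d (kg) | Shift in each arm, p = 0.30 in both | Between-arm, equal switching | Between-arm, p_C = 0.50, p_T = 0.30 | Variance inflation, p = 0.30, SD of change 4 kg |
|---|---|---|---|---|
| 1 | 0.3 kg | 0 | −0.2 kg | 1 + 0.21/16 = 1.01 |
| 2 | 0.6 kg | 0 | −0.4 kg | 1 + 0.84/16 = 1.05 |
| 4 | 1.2 kg | 0 | −0.8 kg | 1 + 3.36/16 = 1.21 |

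The negative sign assumes that the remote method reads higher; the document does not indicate a direction.

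**Could mode differ by arm?** One route is function: the Sample size section assumes a monthly decline of 0.75 units with the intervention against 1.00 in control. A second is calendar time. The first 100 participants are allocated 1:1 and the other 159 are allocated 1:2, which gives 50 + 53 = 103 and 50 + 106 = 156, as stated. About 50/103 = 49% of controls but 50/156 = 32% of intervention participants come from the first period. If the share assessed remotely changed between the periods, the mode mix would differ between arms by about 0.165 times that change. Both routes are conditional, because the article reports no rates of remote assessment or of switching.

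**The case against.** Several points on the other side stand.

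- A reader might infer that a participant who becomes too disabled to travel shows a change that is nothing but a change of method. The article does not support this. The observed change is true change plus any offset, and neither the size nor the direction of an offset is given.
- Inability to attend clinic does not by itself trigger the remote rule. In-person collection at home is offered where feasible, although the article does not say whether the skin fold is then taken. The example given for a missed clinic visit is shielding, and remote collection arose from the COVID-19 redesign. Some participants may be remote throughout and never switch.
- A reader might also expect the extra intervention sessions, held face to face where possible, to make that arm's measurements more often face to face. The Blinding and Study outcomes sections point the other way: intervention staff do not collect outcome measures, a blinded assessor takes these ones, and nothing links the mode of the two kinds of visit.
- Calf circumference is not free of a mode effect. At a remote visit the participant completes the measure with equipment that has been sent, guided by videos and training.
- Equations, mode covariates and sensitivity analyses often belong in the statistical analysis plan, which is not shown and may deal with mode.

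The last point does not remove the concern. The article does not merely leave detail open; it states a rule that makes the estimator follow the visit mode.

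**Conclusion.** The point holds in a limited form. As written, the outcome definition allows two estimators in one participant's series, so change within a participant can be partly a change of method. This rests on the inference that the face-to-face method is not the calf-based one.

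Bias in the treatment comparison needs two further conditions: a systematic difference between the methods, and switching (or mode mix) that differs by arm. If either fails, no bias arises from this source. A systematic offset with equal switching leaves added variance and a shift common to both arms, so the trend within each arm would still be hard to interpret.

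The size cannot be derived from the document. The illustrative between-arm range of 0 to 0.8 kg depends wholly on the assumed offsets and switching shares. The point concerns one derived secondary outcome; calorie intake, weight change and BMI also inform on nutrition, and the ALSFRS-R primary analysis is untouched. It still merits correction, because a single-estimator series is available from measurements already planned.

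**What to change.** For the between-arm longitudinal analysis, derive fat mass and fat-free mass from calf circumference at every visit, whatever the mode, using one stated equation. Record the mode of each assessment (clinic, home in person, video or phone). Because remote calf measurement may itself differ, include mode as a covariate or report a sensitivity analysis by mode. If mode is affected by treatment through function, a covariate adjusts for something that happens after randomisation, so results with and without it should be shown. Report skin-fold-based estimates as supportive, in participants measured face to face both at baseline and at the visit concerned. State whether the skin fold is taken at in-person home visits.

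The cost is wording in the outcome definition and the analysis plan plus one recorded field; no new body measurement is needed. The downside is that skin-fold data do not enter the main estimate, and the article gives no evidence on how well calf circumference alone performs, although it already accepts it as the primary method at remote visits.

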#### Overall survival

Defined as time from randomisation to date of death. Surviving patients will be censored at the date last known to be alive.

#### Total calorie intake

Self-completed by participants via myfood24.org (accessed via the OptiCALS portal). Participants will be asked to complete, and enter, three food diary entries in the week before each study visit. Access to an internet-enabled device will be provided for participants if needed.

#### Change in weight

% weight change throughout the study period.

#### Change in BMI

The BMI calculation divides an adult’s weight in kilograms by their height in metres squared. An existing record of measured height will be used if available in the patient notes. If no measured height is available, this will be taken remotely.

#### Time to gastrostomy

Defined as time from randomisation to date of gastrostomy procedure. If no procedure is recorded patients will be censored at the date last known to be without gastrostomy.

#### Acceptability of the intervention (intervention group only)

Self-reported using a bespoke 11-item questionnaire structured around the Theoretical Framework of Acceptability.^44^

#### Healthcare resource use

A questionnaire to measure use of healthcare services, used in the calculation of the cost-effectiveness of the intervention.

### Adverse events

#### Blood tests

Fasting lipids, albumin, lactate, renal function, thyroid function, neurofilament (Nf) serum, creatinine and C-reactive protein. If face-to-face visits are not possible, these measures will not be taken. The funding for analysis of Nf samples is via separate charitable funding, and as such, samples may be stored and analysed centrally beyond the completion of the trial.

### Safety

AEs may be identified at any point during the study via routine follow-up, contact from the participant and/or carer, on-site or remote monitoring or other sources (medical notes, etc). Participants and/or carers can inform site HCPs of adverse events at any point of the follow-up period. Related serious adverse events (SAEs) will be reported to the Sponsor, Research Ethics Committee and the Project Steering Committee providing safety oversight for the study.

There are no AEs excluded from collection although expected events related to ALS disease progression will not be reported as an SAE, unless the event is more severe than would normally be expected for a participant or if the investigator considers there to be a causal relationship between the trial intervention and the event.

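### For ALS-progression events of expected severity, the only route to SAE status is a causality judgement that in practice only the OptiCALS arm can meet, so by-arm SAE counts built on this rule are not like for like

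*Protocol article*

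**What the plan says.** The Safety section of the protocol article sets three rules.

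- Collection is complete: "There are no AEs excluded from collection".
- SAE labelling is restricted: "expected events related to ALS disease progression will not be reported as an SAE, unless the event is more severe than would normally be expected". The rule has two exceptions, joined by 'or'. The first, at the end of that quote, is severity. The second is causality: "if the investigator considers there to be a causal relationship between the trial intervention and the event".
- Onward reporting depends on relatedness: "Related serious adverse events (SAEs) will be reported to the Sponsor, Research Ethics Committee and the Project Steering Committee providing safety oversight".

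Three other places bear on how these rules work in each arm. Under Usual care, control participants have access only to the food diary and not to the OptiCALS modules. The strengths and limitations box says that neither participants nor investigators can be blinded. Study outcomes takes AEs out of blinded collection: "All outcome measures will be collected by a blinded assessor, except blood samples, calorie intake, adverse events (AEs) and acceptability of the intervention".

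**The concern.** The causality exception refers to the trial intervention. A standard-care participant does not receive it, so in practice an event in that arm cannot be judged related to it. For a progression-type event of expected severity, causality is the only route to SAE status. Whether such an event is labelled an SAE then depends on the arm and on an opinion formed with knowledge of the arm.

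This matters more here than in many trials. The intervention encourages higher oral intake in people whose disease, as the Introduction describes, causes chewing and swallowing problems and ends in respiratory failure. The harms one would most want to look for (choking, aspiration, respiratory deterioration) resemble the exempted progression events. Attributing single cases is a weak way to detect an excess of such events; comparing arms is the stronger one. A by-arm SAE table built on this rule could err in either direction. It would show too many events under OptiCALS if investigators readily attribute them to the diet, and too small an excess if they attribute them to ALS.

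**Working it through.** The document states no SAE rate or expected SAE count, so there is no figure to reproduce. The check has two parts: the rule applied to each arm, and an illustration of scale.

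**The rule by arm, for an expected progression event**

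| Event | Standard care | OptiCALS |
|---|---|---|
| More severe than normally expected | SAE | SAE |
| Expected severity, not judged related | not an SAE | not an SAE |
| Expected severity, judged related to the intervention | cannot in practice arise | SAE |

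Only the third row differs by arm.

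**Scale**

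Arm sizes come from Sample size. The first 100 participants at 1:1 give 50 + 50. The remaining 159 at 1:2 give 53 + 106. The totals are 103 and 156, as stated.

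Let *r* be the risk of a serious progression-type event, *s* the share of these meeting the severity exception, and *f* the share of the remaining OptiCALS events judged related. All three are assumptions.

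- Standard care: 103 × r × s
- OptiCALS: 156 × r × [s + (1 − s) × f]

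*Equal true risk, r = 20%, s = 10%:*

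- Standard care: 103 × 0.20 × 0.10 = 2.1 (2.0%).
- OptiCALS, f = 5%: 156 × 0.20 × (0.10 + 0.90 × 0.05) = 31.2 × 0.145 = 4.5 (2.9%).
- OptiCALS, f = 50%: 31.2 × (0.10 + 0.90 × 0.50) = 31.2 × 0.55 = 17.2 (11.0%).
- OptiCALS, f = 0: 31.2 × 0.10 = 3.1 (2.0%), the same rate as standard care.

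*Other values of r, with s = 10% and f from 5% to 50%:* at r = 10%, 1.0 (1.0%) against 2.3 to 8.6 (1.5% to 5.5%); at r = 30%, 3.1 (3.0%) against 6.8 to 25.7 (4.4% to 16.5%).

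*No event meeting the severity exception, s = 0, r = 20%:* 0 of 103 against 1.6 to 15.6 of 156. This is the extreme case, because it closes the one route that standard-care events have.

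*A true doubling, 20% against 40%, with s = 10% and f = 0:* the true events are 103 × 0.20 = 20.6 and 156 × 0.40 = 62.4. The reported SAEs are 2.1 and 6.2. The ratio of the rates is unchanged, but the risk difference falls from 20 to 2 percentage points and the counts become too small to show the excess reliably.

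**The case against.** The case against has several sound parts.

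- **The severity exception covers both arms.** A reader might infer that a given progression event always counts in one arm and never in the other. The rule does not say that. An unexpectedly severe aspiration under standard care is an SAE, and unrelated events of expected severity are treated alike. The asymmetry is confined to events of expected severity that are judged related.
- **No event is lost.** All AEs are collected, so an arm comparison on all AEs remains possible. Survival, vital capacity and time to gastrostomy are also recorded in both arms whatever the SAE label. This stands, although these outcomes do not replace a comparison of serious events.
- **No by-arm SAE comparison is stated.** The article defers analysis detail to a full statistical analysis plan that is not shown. The absence of a safety table is therefore no fault. The labelling rule, however, is stated, and any SAE count that uses it inherits the problem.
- **Causality-based onward reporting is normal.** Sending related SAEs to the sponsor, ethics committee and steering committee is not itself an error.
- **Committee oversight.** A reader might infer that the Project Steering Committee cannot see an imbalance, since related SAEs are the only flow to it that Safety names. The documents do not support that. Governance gives this committee the data monitoring role, and Randomisation provides for staff who prepare unblinded summaries during the trial. Safety does not say that related SAEs are all the committee receives.

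The exemption could also be read as applying only to individual reporting, which is what the fix asks for. The text does not say so.

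**Conclusion.** The point holds in a limited form. The causality exception is arm-dependent in practice and judged unblinded, so SAE counts for progression-type events may differ by arm without a true difference, or may understate a real one. It is a matter of labelling and reporting and does not show that harms go unrecorded.

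The size cannot be derived from the document. In the central illustration the reported rates are 2.0% against 2.9% to 11.0% with no true difference. This rests on assumed values for event risk, the share qualifying by severity and the share judged related. If investigators judge none related, the rule treats the arms alike and what remains is the loss of events from the SAE count in both. The Sample size section assumes 18% deaths under standard care and 15% under OptiCALS by 12 months, so serious progression-type events are unlikely to be rare.

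The change is worth making because it is cheap and removes the dependence on arm from the harms comparison.

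**What to change.** State in the Safety section that the exemption for expected progression events, with its severity and causality exceptions, governs only individual (expedited) reporting. For summaries to the Project Steering Committee and for the final harms comparison, classify every collected AE by the usual seriousness criteria (death, hospital admission and so on) in both arms, regardless of expectedness or relatedness, and tabulate by arm. Grouping choking, aspiration and respiratory events in that table would make the most relevant comparison visible.

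The cost is a change of wording, a longer SAE listing, some extra coding of seriousness on AEs that are already collected, and one table. If the full protocol or analysis plan already does this, a sentence in Safety saying so is enough.

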### Participant retention

Participant retention is promoted through regular communication from the research team which clearly explains the importance of completing outcome data regardless of study arm. This message is reinforced at enrolment and all follow-up points. A flexible approach to study visits and delivery of intervention also aims to maximise participant retention, including a series of withdrawal options aiming to minimise participant burden, while maximising retention and data collection. Where participants are finding participation in the study challenging, but otherwise want to continue in the trial, options for reduced data collection throughout the remainder of the study will be discussed.

